## Abstract

**Background:**

The oral health of community dwelling frail older people is poor, and depends on the oral health care provisions available within their own community. The implementation project ‘Don’t forget the mouth!’ (i.e.*,* the intervention) was created with the aim of maintaining and improving the oral health and the general health of community dwelling frail older people, with education and interdisciplinary collaborations of health care professionals and informal caregivers. Critical scientific assessment of the intervention will be described in this study protocol, focused on community dwelling older people with dementia.

**Methods:**

This protocol describes a prospective longitudinal single-blind multicentre study, which will take place in 14 towns, each with an intervention and a control group receiving oral health care as usual. Assessment will take place four times during 12 months (i.e.*, at baseline, after 3, 6, and 12 months*). Participants are 65 years and older, community dwelling, and suspected of dementia by their home care worker. The home care organizations will inform, and approach their clients about the study, before the researcher will reach out. The effectiveness of the intervention will be determined with the primary outcome variable ‘oral hygiene’, assessed through the presence of dental plaque (DP) or dental prosthetic plaque (DPP). The secondary outcome variables are: ‘oral health’, ‘oral health related quality of life’, ‘oral health care behaviour’, ‘general health and care dependency’, and ‘compliance of the health care professionals’.

**Discussion:**

This protocol aims to assess the effectiveness of the implementation project ‘Don’t forget the mouth!’ focused on community dwelling older people with dementia. The strengths of the current study are the national roll-out of the intervention, interdisciplinary collaborations and education, and the scientific evaluation over the course of 12 months. The threats and weaknesses are in the recruitment procedure, and the adherence and compliance of the health care professionals to the project.

**Trial registration:**

The Netherlands Trail Register NTR6159.

**Electronic supplementary material:**

The online version of this article (10.1186/s12903-019-0786-5) contains supplementary material, which is available to authorized users.

## Background

Older people are keeping their natural dentition [1] and are staying community dwelling, until high age [2]. The oral health of community dwelling frail older people is poor [3–5], increasing the risks of pneumonia [6], dysregulation of diabetes mellitus [7], and heart and cardiovascular diseases [8]. Additionally, poor oral health can impair mastication [9–11], which can be associated with malnutrition [10, 12], and cognitive decline [9, 10, 13].

Older people with dementia compared to people without dementia have poorer oral health, characterized by, amongst others, larger amounts of oral plaque and calculus, higher prevalence of mucosa deviations, presence of (root)caries, and an increased dental treatment need [5, 12, 14–16]. On top of that the frequency of visits to an oral health care professional decreases [14]. When older people become care dependent, e.g.*,* as with dementia, caregivers often do not have enough knowledge about how to provide oral hygiene care, nor do they have the proper skills to provide it [17, 18]. Inadequate prioritising and providing oral hygiene care by home care workers, case managers and physicians causes decline of oral health of people with dementia [3]. While the demand increases for (professional) oral health care in the community, the current oral health care system is not prepared to provide [11, 19, 20].

In 2014, a Dutch study [21] highlighted that although some promising national interventions were developed to improve oral health care of older people in nursing homes, only a few have focused on improving this aspect for community dwelling older people. In addition, the authors of the study strongly recommended scientifically evaluating all future interventions [21].

The implementation project ‘Don’t forget the mouth!’ was developed with the aim of maintaining and improving the oral health and the general health of community dwelling frail older people with education, and interdisciplinary collaborations of: physicians, general practice nurses, dentists, dental hygienists, case managers, district nurses, home care workers (i.e.*, health care professionals*), and informal caregivers.

Critical scientific assessment of this implementation project is described in this study protocol, focused on community dwelling older people with dementia.

## Methods and design

### Study design

This protocol describes a prospective longitudinal single-blind multicentre study, which will take place in 14 towns in the Netherlands. Recruitment will take place in two districts within a town, i.e.*, an intervention group* and *a control group*, that are matched based on social-economic status and population composition, and are enrolled through the town’s home care organization. Assignment of a district to the intervention or the control group will be done ‘a priori’. The intervention group will receive care of the healthcare professionals who participate in the implementation project ‘Don’t forget the mouth!’. The control group will receive care as usual. The participants will be visited at their home for assessment, at baseline, after 3, 6, and 12 months. The health care professionals of the intervention group will receive questionnaires. All data collection will be done by the same blinded researcher, viz., a dentist trained in the geriatric dentistry. Participants will be blinded. Health care professionals participate in the intervention, and therefore they cannot be blinded. The blinding code can be broken by the supporting investigator (RW) or principal investigator (FL) in case of a medical emergency of a participant. The Data Safety Monitoring Board (DSMB) is not needed because the risk for adverse side effects in this study is determined to be negligible. An independent monitor will monitor the study data according to ‘Good Clinical Practice’(GCP).

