##### Dental prosthesis plaque

The DPP will be classified according to the Augsburger and Elahi index [30]. In this method, the maxillary RDP will be rinsed, coloured with a disclosing solution, a score will be given to each of the eight planes (score range 0–4, 0 = 0% plaque, 1 = 1–25% plaque, 2 = 26–50% plaque, 3 = 51–75% plaque, and 4 = 76–100% plaque, visible) [30], and a total score will be calculated. As disclosing solution, 0.05% methylene blue (produced by pharmacy ‘De Tolgaarde’, Leusden, Netherlands) will be used. In the current study, the assessment of the mandibular RDP has been added. The DPP score will be averaged in case there are two RDPs (an maxillary and a mandibular). To facilitate reproducibility, the RDP will be placed on a specially designed reference sheet with a grid outline indicating the planes. The RDP is then photographed with a dental camera (Shofu, Eye special II, Ratingen, Germany). A pilot study showed excellent inter-rater, and intra-rater agreement for both the maxillary and mandibular RDP assessments with the described method, when performed by trained and calibrated researchers (data not yet published).

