#### Oral health care behaviour

Information about the oral health care behaviour of the participants will be collected through two questionnaires designed for this study. The first questionnaire contains twelve items for the participant about daily oral hygiene care, difficulties with oral hygiene care, and visits to an oral health care professional. The second questionnaire contains fourteen items for the informal caregiver about their role, knowledge, and difficulties with oral health care of the participant.

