#### Compliance of the health care professionals

To explore how the intervention is carried out, the compliance of the health care professionals will be assessed with questionnaires specifically designed for this study. There are six different questionnaires, three versions at baseline and three versions for the follow-up phase. There is one version for the health care professionals at the general practice, one version for the health care professionals at the dental practice, and one version for health care professionals of the home care organization. The questionnaires at baseline contain nine (home care organization) or ten (general practice and dental practice) items, about their care population, collaborations with other health care professionals, oral health care education, and oral health care organization in the practice or organization for frail older people.

The follow-up questionnaires contain eight (general practice) or nine (dental practice and home care organization) items, about the same subjects as mentioned at baseline; the item describing their care population will be left out.

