## Discussion

This protocol describes a prospective longitudinal single-blind multicentre study, which aims to assess the effectiveness of the implementation project ‘Don’t forget the mouth!’ focused on community dwelling older people with dementia.

As any study, this protocol has some specific strengths, weaknesses, threats, and opportunities, which will be lined out below.

The strengths of the current study are the national roll-out of the intervention, interdisciplinary collaborations and education of different health care professionals focused on knowledge, attitude and skills of oral health care, and the scientific evaluation over the course of 12 months. According to the sample size calculation 11 towns are needed for this study, while the implementation project ‘Don’t forget the mouth!’ will take place in 14 towns, providing margin for withdraws.

The possible weaknesses of assessing the effectiveness of the implementation project are selection bias from allocation, due to recruitment through the home care organization. Randomization of the districts was not possible in the described study. Participants will not explicitly be made aware of their allocation, but some will be aware of the intervention as they are receiving educational materials through their health care professionals. Another possible weakness is the fact that the GOHAI-NL is not validated for people with dementia [34]. At the time of writing the protocol, there were no validated questionnaires available to assess OHRQoL for people with dementia. The reliability of the answers of the GOHAI-NL will be increased through taking, if needed, additional information from informal caregivers to account [34]. The two questionnaires about oral health care behaviour and compliance of the health care professionals are designed for this study, and not validated, which is a weakness of these instruments.

Within the current study, there is an opportunity to additionally assess the process of the implementation. If process evaluation can be conducted, recommendations about success factors or thresholds with implementation can be made to health care professionals.

The threats are found in the recruitment procedure (through the home care organisation), different informal caregivers with each assessment, and the adherence and compliance of the health care professionals to the intervention.

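### The blinded plaque assessor is also assigned all data collection, including questionnaires that only intervention staff receive

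*Protocol article*

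**What the plan says.** The Study design section of the Protocol article has two adjoining sentences. The first is "The health care professionals of the intervention group will receive questionnaires"; no control-group version is mentioned there or elsewhere. The second is "All data collection will be done by the same blinded researcher", who is a dentist with geriatric training. No other data collector is named. The same section fixes allocation in advance by district, two per town, places the assessments in participants' homes at four time points, and states that participants are blinded.

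Other sections bear on this:

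- **Compliance of the health care professionals:** "the compliance of the health care professionals will be assessed with questionnaires specifically designed for this study". There are versions for general practice, dental practice and home care, each at baseline and follow-up.
- **Oral health care behaviour:** the participant questionnaire covers "daily oral hygiene care, difficulties with oral hygiene care, and visits to an oral health care professional". A second one asks informal caregivers about their role, knowledge and difficulties.
- **Dental plaque (DP):** graded 0–3 with mirror and probe.
- **Dental prosthesis plaque (DPP):** each plane graded 0–4 after disclosing. "The RDP is then photographed with a dental camera", but no masked reading of the photographs is stated.
- **Discussion:** participants are not explicitly told their allocation, but "some will be aware of the intervention as they are receiving educational materials through their health care professionals".

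**The concern.** A form sent only to intervention staff identifies its sender as intervention staff. If the plaque assessor handles those forms, the assessor can learn which practices, and hence which districts, are intervention. Staff forms exist at baseline as well as follow-up, so this could happen early.

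Both primary measures rest on an examiner's grading, and one person grades everyone. Any expectation effect would therefore run in one direction and would not average out over raters. The Discussion already concedes possible selection bias and that districts could not be randomised, so masked assessment is one of the main safeguards left. The good rater agreement reported from the pilot concerns denture scoring and says nothing about knowledge of arm.

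**Working it through.** The plan gives no figure for this point, so the check is a comparison of sections.

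**Step 1: the direct conflict.** Staff questionnaires go to the intervention group only, and all data collection belongs to the blinded researcher. Taken together, the blinded researcher collects intervention-only forms. The wording contains no exception.

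**Step 2: from a form to a participant's arm.** Allocation is by whole district, and home visits show the assessor which district a participant lives in. Linking one practice to the intervention can therefore reveal the arm of a district and, with two matched districts per town, of its comparator. The link is strongest for the general practice and dental practice forms. It is weaker for home care forms, because both districts of a town are enrolled through that town's home care organization.

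**Step 3: further routes at the visit.** The participant questionnaire asks about oral hygiene and "visits to an oral health care professional", and the caregiver questionnaire asks about knowledge. These are matters the intervention tries to change. Some participants will know of the project. None of this fixes the arm with certainty, but each item can hint at it.

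**Step 4: protective steps described.** The article describes no separate handler for staff forms, no rule that plaque is scored first and no masked reading of the denture photographs. For DP no photograph is described at all.

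**Step 5: illustration of the stakes only.** Inputs from the Sample size section: SD 0.75 (DP) and 0.88 (DPP); differences 2.17 − 1.63 = 0.54 and 2.13 − 1.60 = 0.53; α = 0.05; power 80%. Taking the test as two-sided:

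- n per group = 2σ²/δ² × (1.960 + 0.842)² = 30.3 for DP and 43.3 for DPP, that is 31 and 44.
- With the plan's 10% added: 30.3 × 1.1 = 33.3 (stated 34) and 44 × 1.1 = 48.4 (stated 49). The stated figures reproduce apart from how they are rounded.

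Now assume that there is no true effect and that scoring differs between arms by b points. The value of b is an assumption; the documents give none. With SE = σ√(2/n), SE = 0.75 × √(2/31) = 0.190 for DP and 0.88 × √(2/44) = 0.188 for DPP. The two-sided rejection rate is 1 − Φ(1.96 − b/SE) + Φ(−1.96 − b/SE):

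| Assumed b | DP, 31 per group | DPP, 44 per group |
|---|---|---|
| 0.1 | 8% | 8% |
| 0.2 | 18% | 19% |
| 0.3 | 35% | 36% |

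For scale, 0.1 and 0.2 points are 0.1/0.54 = 19% and 0.2/0.54 = 37% of the planned DP difference. The table ignores clustering and uses a normal approximation, whereas the plan uses rank tests.

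**The case against.** The best defence is that this is a condensed article. It says that staff receive questionnaires, not who sends, opens or reads them. They could be coded or completed online, and the full protocol may separate the tasks. That stands against the claim that blinding is bound to fail, which a reader might infer and which the text does not show. It does not remove the conflict: the article is not silent but assigns all data collection to the blinded researcher. If the tasks are separated, that sentence is wrong.

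Several other stronger readings also go beyond the text:

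- **Oral care interviews by the assessor.** The article speaks of questionnaires and does not say how they are given. Control participants also clean their teeth and see dentists, so answers need not reveal the arm.
- **Home care organizations identified as intervention.** One organization serves both districts of a town, so its name alone does not reveal the arm.
- **The assessor applies the control-only exclusion.** That rule, under Participants, requires knowing the arm and the intervention practices, but nobody is named as applying it.
- **Project materials prove the arm.** The Intervention section makes them available online and for frail older people generally.
- **A concealed failure of participant blinding.** The Discussion discloses the awareness as a weakness. What remains is that the flat statement in Study design should match it.
- **A known false-positive rate.** The scoring difference in the illustration has no source in the documents.

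**Conclusion.** The point holds as an internal conflict in the Study design section. If the wording is followed, the person who grades the primary outcome is exposed to information that can reveal the allocation. A stated procedure therefore undermines a stated safeguard, and this is more than a missing detail. The oral care questionnaires and participants' awareness increase the risk.

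The conclusion assumes that all data collection means what it says and includes the staff forms. It does not establish that the assessor will be unmasked or that the scores will be biased. The size of any bias cannot be derived from the document, and the table above shows only what an assumed scoring difference would do. The plan should be corrected, because the outcome is examiner-graded, the districts are not randomised and the remedy is cheap.

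**What to change.** 1. Replace the sentence on all data collection with wording such as: *Plaque and other participant assessments will be done by one researcher kept unaware of allocation. This researcher will not send, receive or read the staff questionnaires, which will be handled by the supporting investigator.* That investigator may already break the blinding code.
2. Keep the list of intervention practices, and the check of the control-only exclusion, away from the assessor.
3. At each visit, score plaque before any oral care questionnaire.
4. Score DPP from the photographs already taken, coded and shuffled across arm and visit.
5. Record the assessor's guess of arm and report it.
6. Align the statement in Study design that participants are blinded with the Discussion.

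**Cost.** Tasks move within the existing team, the order of the visit is fixed, and coding and reading photographs takes modest extra time.

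**What remains.** Scoring first at one visit does not undo what was learned at an earlier one, and no DP photographs are described. DP is therefore only partly protected at follow-up, and its assessor blinding should be described as attempted, not assured.

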### Participants

The inclusion criteria are: community dwelling people aged 65 years or older; a Mini Mental State Examination (MMSE, a short screening instrument which assesses general cognition, awareness, and memory [22]) score between 18 and 24, which in this study will be considered indicative of dementia [23, 24], and receiving care from health care professionals of the participating home care organization and general practice. Exclusion criteria are: suffering from a terminal illness; having a MMSE score lower than 18 or higher than 25; and being edentulous without prosthesis. Additionally, the participants in the control group will be excluded if they are registered at the general or dental practice of the intervention group.

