### Health care professionals

In this study, the physicians, general practice nurses, dentists, dental hygienists, case managers, district nurses, and home care workers will be referred to as health care professionals. In order to be eligible to participate in this study, a health care professional, practice, or organization must also meet several inclusion and exclusion criteria. The inclusion criteria are: willing to include oral health care in the practice organization; the health care professional in the general health practice is willing to use validated frailty questionnaires [25–27]; the dentist has affinity with older people; the dental practice is accessible for older and/or disabled people [28]; and the health care professional of the home care organization is willing to make an inventory of the oral health care needs of their clients. The exclusion criteria are: temporary position of a health care professional; and providing only care to a population younger than 65 years.

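### Dental-practice registration is an exclusion in the control arm but is not considered in the intervention arm; it should be recorded in both arms and the plaque comparison stratified by it (minor, cheap improvement)

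*Protocol article*

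**What the plan says.** Under Participants, the provider criterion for entry is "receiving care from health care professionals of the participating home care organization and general practice". It names no dental practice. Of the exclusions common to both arms, none concerns dental registration; apart from terminal illness they are "having a MMSE score lower than 18 or higher than 25; and being edentulous without prosthesis". One further exclusion applies to controls alone: "the participants in the control group will be excluded if they are registered at the general or dental practice of the intervention group".

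Under Study design, "The intervention group will receive care of the healthcare professionals who participate in the implementation project". Under Health care professionals, that group is defined broadly: "the physicians, general practice nurses, dentists, dental hygienists, case managers, district nurses, and home care workers will be referred to as health care professionals". Read together, these describe an intervention group that is cared for by project dentists among others, but neither sentence is an eligibility rule.

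The two districts of a town are "matched based on social-economic status and population composition, and are enrolled through the town’s home care organization". The Discussion adds that "Randomization of the districts was not possible in the described study". It acknowledges selection bias through home care recruitment but does not mention dental registration. Under Statistical analysis, the effect of group over time is tested with Kruskal-Wallis, and no covariate or stratum is named.

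**The concern.** General practice appears both in the entry rule and in the control exclusion. Dental practice appears only in the control exclusion. By excluding controls on this ground, the plan accepts that the project's dental practice is a route of exposure, yet it does not ask about that route when it admits an intervention participant.

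Two things follow. First, patients of the project's dental practice are removed from one arm and kept in the other. The control arm then holds a somewhat larger share of people with no dentist. The Background says that in dementia "the frequency of visits to an oral health care professional decreases", so it is reasonable to expect some people without regular dental care. If they have more plaque, the controls look worse for a reason unrelated to the project, and the contrast is tilted towards the intervention.

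Second, the criteria admit intervention participants with an outside dentist or none, while Study design describes the group as cared for by project professionals, who include dentists. The reader cannot tell which of the two defines the group.

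**Working it through.** **The plan's own figures.** Planned difference in dental plaque (DP): 2.17 − 1.63 = 0.54, SD 0.75. For prosthesis plaque (DPP): 2.13 − 1.60 = 0.53, SD 0.88. With two-sided alpha 0.05 and 80% power, f(α, β) = (1.960 + 0.842)² = 7.85.

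- DP: 2 × 0.75² / 0.54² × 7.85 = 30.3; × 1.1 = 33.3, so 34.
- DPP: 2 × 0.88² / 0.53² × 7.85 = 43.3, rounded up to 44; × 1.1 = 48.4, so 49.
- Towns, DP: 2 × 34 × (1 + 7 × 0.03) / 8 = 10.3.
- Towns, DPP: 2 × 49 × (1 + 11 × 0.03) / 12 = 10.9, so 11.

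The stated 34, 49 and 11 reproduce. None of them depends on dental registration, so this point does not challenge them.

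**Shift in the registration mix.** The documents give no registration shares, so the inputs are assumptions:
- p = share of clients registered with any dentist, equal in both districts;
- f = share of control-district registrants who use the project's dental practice.

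The exclusion removes a fraction p × f of control-district clients, all of them registered. The unregistered share is then (1 − p) / (1 − p × f) in the control arm and 1 − p in the intervention arm. The last two columns assume that unregistered people score 0.5 DP points worse.

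| p | f | Control | Intervention | Gap (points) | Shift in DP | Shift / 0.54 |
|---|---|---|---|---|---|---|
| 0.8 | 0.1 | 0.2 / 0.92 = 21.7% | 20% | 1.7 | 0.009 | 1.6% |
| 0.6 | 0.3 | 0.4 / 0.82 = 48.8% | 40% | 8.8 | 0.044 | 8.1% |
| 0.5 | 0.4 | 0.5 / 0.80 = 62.5% | 50% | 12.5 | 0.0625 | 11.6% |

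Against the SD of 0.75, the shift is 0.01 to 0.08 SD. The top row of that range needs 40% of registered people in the control district to be patients of the project's practice. With the same assumed 0.5-point penalty on DPP, the largest shift is 0.0625 / 0.53 = 11.8% of the planned difference.

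**Would a mirrored exclusion help?** Suppose intervention-district clients of outside dentists were also excluded and those with no dentist kept. With g = share of intervention-district registrants at the project's practice (assumption), the unregistered share there becomes (1 − p) / (1 − p × (1 − g)). At g = 0.3:

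- p = 0.8: 0.2 / 0.44 = 45.5%, against 21.7% in controls;
- p = 0.6: 0.4 / 0.58 = 69.0%, against 48.8%;
- p = 0.5: 0.5 / 0.65 = 76.9%, against 62.5%.

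Gaps of about 24, 20 and 14 points replace 1.7, 8.8 and 12.5, with the sign reversed. Balance would need g = 1 − f, which nothing ensures.

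**The case against.** The strongest reply is that a contamination rule is one-sided by nature. Both districts lie in one town, so a control client of the project's dental practice would be exposed, while an intervention client of another dentist contaminates nothing. That stands, and it is why the exclusion should stay.

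A reader might infer that dental attenders as such are removed from the control arm. The text does not say so. Only people registered at the intervention group's own practice are lost, and controls with any other dentist remain. Registration is also not the same as attendance; the Background speaks of falling visit frequency, not of registration.

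A reader might also infer that intervention participants without a project dentist cannot receive the intervention, and that the planned effect is diluted. If half had no project dentist and the dental part carried a quarter to a half of the effect, 0.54 would become 0.54 × (1 − 0.5 × 0.25) = 0.47 or 0.54 × (1 − 0.5 × 0.5) = 0.41. The documents do not support this. The Intervention section describes education, early recognition of declining daily hygiene, and a referral tool for all professionals, so home care and general practice deliver much of it, and people without a dentist are natural candidates for referral. Under Sample size, the 25% reduction is set as a clinically relevant effect. It is not presented as an estimate among people with a project dentist, so no stated figure is there to be diluted.

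Finally, a standing difference in plaque would show in the planned baseline comparison, dental visits are already asked about in the behaviour questionnaire, and an article may leave recording details to the full protocol. These points lower the severity. They do not remove the one-sided rule, which the article itself states, and seeing a baseline imbalance is not the same as allowing for it.

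**Conclusion.** The point holds in a limited form. Dental-practice registration selects people out of the control arm only, and nothing stated balances it: allocation is not randomised, matching covers other factors, and the named test is unadjusted. The effect on the contrast is probably small, about 0.01 to 0.06 DP. That range rests wholly on assumed registration shares, overlap and plaque penalty, because the document gives none of them. The direction, towards the intervention, assumes that people without a dentist have more plaque.

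The intervention arm may, not must, contain people without a project dentist. This is not an error in itself, but the Study design description and the Participants criteria need to be reconciled. The documents do not support a claim that the trial loses power or that its effect is diluted. Severity is minor; this is a cheap improvement.

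**What to change.** 1. Keep the control exclusion. Do not add a mirrored exclusion for the intervention arm: as shown above, it can widen the imbalance. It would also cost eligible participants, and the margin of 14 towns over 11 is already assigned in the Discussion to withdrawals.
2. At baseline, in both arms, record whether the participant's dental practice is the project's, another or none.
3. Stratify the between-group oral hygiene comparison by registered versus not registered at baseline, for example with a stratified rank test (van Elteren).
4. As a sensitivity analysis, repeat the contrast with intervention participants limited to those whose dental practice is not outside the project. Keep the same strata, because this restriction by itself changes the registered share.
5. Reconcile Study design with Participants: say whether care by a project dentist is part of the definition of the intervention group or only one component that may be offered.

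The cost is one extra screening item and a slightly more complex analysis; no recruitment is lost. One limit remains: within the registered stratum, patients of the project's practice are still found only in the intervention arm. Stratification removes the shift in the registered share but not any difference between those patients and patients of other dentists.
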